## Abstract

**Background:**

Caregivers of patients with severe acute brain injuries (SABI) that lead to coma and require intensive care unit (ICU) treatment often experience chronic emotional distress. To address this need, we developed the Coma Family (COMA-F) program, a mindfulness-based resiliency intervention for these caregivers.

**Objective:**

We will conduct an open pilot trial of COMA-F (National Institutes of Health Stage IA). Here we describe our study protocol and proposed intervention content.

**Methods:**

We will enroll 15 caregivers of patients with SABIs during their loved one’s hospital course from 3 enrollment centers. A clinical psychologist will deliver the COMA-F intervention (6 sessions) over Zoom (Zoom Video Communications, Inc) or in person. We will iterate COMA-F after each caregiver completes the intervention and an exit interview. English-speaking adults who have emotional distress confirmed by the clinical team and are the primary caregivers of a patient with SABI are eligible. The adult patient must have been admitted to the neuro-ICU for SABI and (1) have had a Glasgow Coma Scale score below 9 while not intubated or an inability to follow meaningful commands while intubated at any point during their hospitalization for >24 hours due to SABI; (2) will be undergoing either tracheostomy or percutaneous endoscopic or surgical gastrostomy tube placement or have already received one or both; and (3) have a prognosis of survival >3 months. We will identify eligible caregivers through screening patients’ medical records and through direct referrals from clinicians in the neuro-ICU. During the intervention we will teach caregivers mind-body and resilience skills, including deep breathing, mindfulness, meditation, dialectical thinking, acceptance, cognitive restructuring, effective communication, behavioral activation, and meaning-making*.* Caregivers will complete self-report assessments (measures of emotional distress and resilience) before and after the intervention. Primary outcomes are feasibility (recruitment, quantitative measures, adherence, and therapist fidelity) and acceptability (treatment satisfaction, credibility, and expectancy). We will conduct brief qualitative exit interviews to gather feedback on refining the program and study procedures. We will examine frequencies and proportions to determine feasibility and acceptability and will analyze qualitative exit interview data using thematic analysis. We will also conduct 2-tailed *t* tests to explore signals of improvement in emotional distress and treatment targets. We will then conduct an explanatory-sequential mixed methods analysis to integrate quantitative and qualitative data to refine the COMA-F manual and study procedures.

**Results:**

This study has been approved by the institutional review board at 1 of the 3 enrollment centers (2023P000536), with approvals at the other 2 centers pending. We anticipate that the study will be completed by late 2024.

**Conclusions:**

We will use our findings to refine the COMA-F intervention and prepare for a feasibility randomized controlled trial.

**Trial Registration:**

ClinicalTrials.gov NCT05761925; https://clinicaltrials.gov/study/NCT05761925

**International Registered Report Identifier (IRRID):**

PRR1-10.2196/50860

## Introduction

### Background

Severe acute brain injuries (SABI) such as ischemic stroke, hemorrhagic stroke, traumatic brain injury, or hypoxic-ischemic encephalopathy are sudden catastrophic events for both patients and their families [1]. The majority of patients with SABI cared for in an intensive care unit (ICU) are incapacitated, and many are comatose [2]. Caregivers of patients with SABI who survive their ICU admission nevertheless experience high rates of emotional distress, which, if untreated, becomes chronic [1,3]. These caregivers grapple with the uncertainty of their loved one’s long-term prognosis, the stress of making decisions on their loved one’s behalf, grief over their loved one’s loss of neurological function, and the stress of managing their own life outside of the ICU [1,3,4]. While the stay in an ICU itself can be quite lengthy, ultimate recovery from SABI can be prolonged and uncertain, and caregivers often endure these stressors beyond the acute hospitalization [5,6].

Caregivers of hospitalized patients with SABI have unmet needs for emotional support. Prior work shows that they feel overwhelmed, underprepared for caregiving, unable to manage basic self-care, isolated, and lonely, and that they deal with ambiguous loss [5-8]. Despite these needs, a recent systematic review found that among 22 interventions for caregivers to general ICU patients, none led to long-term improvements in emotional distress, and many actually increased caregiver burden [9]. Further, there are few interventions specific to the needs of SABI caregivers. Those that do exist focus mainly on crisis management and decision-making during the initial 48 hours of admission [3,10,11] rather than addressing prolonged uncertainty, grief, and stress. Taken together, there is a critical need for effective interventions for caregivers of surviving patients with SABI that extend into the period following the ICU stay.

Our team has followed the National Institutes of Health (NIH) Stage Model for behavioral intervention development [12] to develop the Coma Family Program (COMA-F), a mindfulness-based resiliency program for caregivers of patients with SABI transitioning out of the ICU (Figure 1). We developed preliminary COMA-F content based on adaptations of our intervention for patients and caregivers hospitalized in the neuro-ICU (Recovering Together) [13] and from qualitative interviews of caregivers of surviving patients with SABI. For the latter, we conducted longitudinal qualitative interviews with 30 caregivers across 14 ICUs in the United States to better understand their stressors, coping methods, and treatment preferences [14,15]. Nearly all caregivers discussed using avoidance or distraction as initial coping strategies [14]. They also expressed a desire to learn adaptive coping skills, learn communication skills for interacting with the patient’s care team and other family members, and for support with making difficult decisions (Hwang et al, “Psychosocial support needs and preferences among family caregivers of ICU patients with severe acute brain injury: a qualitative thematic analysis,” manuscript under review). We have used this feedback and adapted content from Recovering Together to develop the first version of the COMA-F intervention. We plan to deliver COMA-F through a single-arm open pilot trial outlined in this paper (N=15 caregivers). We will use the findings from the open pilot to iteratively refine COMA-F. We will then conduct a feasibility randomized controlled trial (RCT) of COMA-F versus minimally enhanced usual control (MEUC).

**Figure 1 figure1:**
[figure not shown]
Iterative stages of the development of a mind-body resiliency program for caregivers of patients with severe acute brain injury (the COMA-F program). The open pilot trial described in this protocol is outlined in bold. The subsequent feasibility RCT and efficacy RCT are outlined by dashed lines. COMA-F: Coma Family program; MEUC: minimally enhanced usual control; RCT: randomized controlled trial; SABI: severe acute brain injury.

### Objectives

Here we describe our procedure and delivery of the COMA-F open pilot trial. We will explore the preliminary feasibility and acceptability of COMA-F. Further, through exit interviews at the end of the intervention, we expect to elicit feedback on program procedures (hybrid in-person and Zoom format), treatment manuals, support from study staff, and expectations of the program. We will use this feedback to inform each iteration of COMA-F. After completion of the open pilot trial, we will then proceed to test the feasibility of the refined COMA-F program versus the MEUC.

## Methods

### Study Design and Setting

We will deliver our open pilot of COMA-F for caregivers of comatose patients with SABIs enrolled from 3 academic medical centers in the United States. If we encounter recruitment challenges, we will also plan to enroll from collaborators’ institutions in the northeastern and mid-Atlantic regions of the United States. We present our study design and procedure in Figure 2.

**Figure 2 figure2:**
[figure not shown]
Open pilot trial design and procedure for the development of a mind-body resiliency program for caregivers of patients with severe acute brain injury (the COMA-F program). COMA-F: Coma Family; REDCap: Research Electronic Data Capture.

### Ethics Approval

This study has been approved by the institutional review board at 1 of the 3 enrollment centers (Mass General Brigham Institutional Review Board, 2023P000536), with approvals at the other 2 centers pending. We will conduct informed consent with all caregivers enrolled in the study. We will deidentify all data and provide subject ID numbers to participants. We will compensate participants US $20 via check for completing baseline assessments and US $40 via check for postintervention assessments, for a total of US $60 per participant.

### Recruitment and Screening

#### Overview

We present our study inclusion criteria in Textbox 1. We will recruit caregiver subjects through 2 concurrent mechanisms.

Open pilot trial inclusion criteria for the development of a mind-body resiliency program for caregivers of patients with severe acute brain injury (the Coma Family program).Age 18 years or olderEnglish-speakingScreens for emotional distress on either depression or anxiety subscales (>7) of the Hospital Anxiety and Depression ScaleConfirmed by the primary clinical team as the primary caregiver for a patient who has the following characteristics:Age 18 years or olderAdmission to the intensive care unit with a severe acute brain injury for one of the following: ischemic stroke, intracerebral hemorrhage, subarachnoid hemorrhage, traumatic brain injury, or hypoxic-ischemic encephalopathyGlasgow Coma Scale score below 9 (in the judgment of the medical team) while not intubated or an inability to follow meaningful commands while intubated at any point during their hospitalization course for more than 24 consecutive hours due to the brain injury itself and not a confounding factor (ie, sedation and seizures)Still alive in the intensive care unit at the time that the clinical team approaches the primary caregiver about possible recruitmentEither will be undergoing tracheostomy and percutaneous endoscopic or surgical gastrostomy tube placement or has already received one or bothHas a prognosis for survival of greater than 3 months and does not have a concurrent diagnosis of a terminal illness or injury, as judged by the clinical team

#### Referrals From the Clinical Team

ICU medical and nursing team members who are caring for patients with SABIs will identify eligible caregivers and notify the study team, as they currently do in 1 of our enrollment centers for our ongoing Recovering Together trial of patients and caregivers in the neuro-ICU [13]. Notably, COMA-F will capture caregivers of patients with SABI as described in Textbox 1, whereas Recovering Together exclusively focuses on dyads of caregivers and patients who are cognitively intact.

#### Study Staff Screening

We will conduct daily prescreening of electronic health record admission reports to identify patients that meet the SABI criteria discussed below. Study staff will then inquire with the clinical team if the identified patients have a caregiver that meets inclusion criteria.

### Enrollment

Once a potential caregiver has been identified and approved by the clinical team, a member of the study team will approach the caregiver in person or call them via phone no later than 7 days after the patient’s transfer to a lower level of care.

Caregivers who wish to participate will complete consent. During the consent process we also inform caregivers that we will collect patient data from the medical record (eg, demographics, diagnosis, and procedures). Prior to the intervention, caregivers will complete self-report baseline assessments through Research Electronic Data Capture (REDCap) either in person on a tablet, or they will be emailed a link to the REDCap survey. We plan to enroll 15 caregivers.

### COMA-F Intervention Content

The intervention will have 6 sessions and be presented as a hybrid program. Caregivers will have the option for any number of initial sessions to be delivered in person within the hospital (until the patient is discharged). If the patient is discharged at any point in the intervention, the remaining sessions will be delivered via live video using Zoom. We will also give caregivers the option of completing the intervention completely over Zoom. Zoom is a free and secure internet-based videoconferencing software program that is currently used to provide care for patients at each of the recruiting centers.

Sessions focus on developing mindfulness-based resiliency skills to cope with and manage caregiver-related stressors. The sessions were developed based on caregiver feedback in our qualitative interviews [14,15] and from adapted Recovering Together content [13]. Caregivers will choose 6 modules from a selection of 7 modules. The 7 modules are presented in Table 1.

**Table 1 table1:** Session outline for the COMA-F^a^ program. The program will be delivered to caregivers of patients with severe acute brain injuries. The program will take place over 6 weeks.

Session	COMA-F topic	COMA-F skills and session content
1	Coping with the here and now	Deep breathing, mindfulness, 24-hour block, and mindfulness meditation
2	Coping with uncertainty	Dialectics, hands as worries, and support with difficult decisions
3	Adjusting to new roles	Identify the distress spiral and challenge unhelpful thoughts
4	Engaging social support	Effective communication with other family members and friends and care team
5	Engaging with positive activities	Behavioral activation, using social support, and setting daily goals
6	Managing fear and worry	Observing fear and worry and acceptance and change
7	Making meaning from our experiences	Making meaning: finding purpose and meaning in new caregiving role

^a^COMA-F: Coma Family.

### Feasibility and Acceptability Outcomes

The feasibility and acceptability markers are presented in Table 2.

**Table 2 table2:** Feasibility and acceptability outcomes for our open pilot trial of a mind-body resiliency program for caregivers of patients with severe acute brain injuries. Outcomes will be assessed at the end of the program.

Outcome		Definition
**Feasibility (>70% acceptable; >80% excellent)**		
	Recruitment	Percentage of eligible caregivers who participate
	Assessments	Percentage of enrolled caregivers with no measures missing
	Adherence	Percentage of caregivers that complete 4 of 6 sessions
	Therapist fidelity	After randomly selecting 20% of sessions, percentage of sessions with 100% of content delivered
**Acceptability (>70% acceptable; >80% excellent)**		
	Treatment satisfaction	Percentage of caregivers who score above the midpoint on the Client Satisfaction Questionnaire-3 [16]
	Credibility and expectancy	Percentage of caregivers who score above the midpoint on Credibility/Expectancy Questionnaire [17]
	Adverse events	Mild adverse events reported in <10% of caregivers; no adverse events linked to program participation

### Assessments

We selected quantitative measures based on those collected in Recovering Together and from our qualitative interviews during COMA-F development (Textbox 2). We will administer the same measures at baseline and after the intervention.

Quantitative measures administer at baseline and after the intervention.
**Emotional distress**
Hospital Anxiety and Depression Scale—measures anxiety and depression symptoms [18]; Posttraumatic Stress Disorder Checklist–5—measures posttraumatic stress symptoms [19].
**Resiliency factors**
Measure of Current Status Part A—measures adaptive coping abilities [20]; Cognitive and Affective Mindfulness Scale Revised—measures inclination toward acting mindfully [21]; Toronto Mindfulness Scale–Trait—measures trait mindfulness [22]; ENRICHD Social Support Instrument—measures perceived availability of social support [23].
**Functional status of patient**
Barthel Index—measures functional independence in activities of daily living [24]; Modified Rankin Scale—measures level of disability in patients after a SABI [25].

### Exit Interview Procedures

Caregivers will complete the postintervention measures listed above immediately after the end of session 6. We will then conduct a brief 5-10 minute exit interview. We will ask caregivers to provide feedback on the program procedures, hybrid in-person and Zoom format, treatment manuals, support from study staff, and expectations of the program. We will also ask caregivers to discuss their responses on the pre- and postintervention assessments.

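### Post-intervention measures and exit interviews are scheduled only after session 6, so caregivers who stop early, including those counted as adherent at 4 sessions, have no scheduled acceptability, change or feedback data

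*Protocol article*

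**What the plan says.** Exit Interview Procedures sets one time point for post-treatment data: "Caregivers will complete the postintervention measures listed above immediately after the end of session 6". The interview comes directly afterwards: "We will then conduct a brief 5-10 minute exit interview". The Methods paragraph of the Abstract ties refinement to the same event: "We will iterate COMA-F after each caregiver completes the intervention and an exit interview". The caption of Table 2 says of the feasibility and acceptability markers: "Outcomes will be assessed at the end of the program".

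Three rows of Table 2 matter here:
- Adherence: "Percentage of caregivers that complete 4 of 6 sessions".
- Assessments: "Percentage of enrolled caregivers with no measures missing".
- Treatment satisfaction: "Percentage of caregivers who score above the midpoint on the Client Satisfaction Questionnaire-3". The credibility and expectancy row is worded in the same way.

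These markers are judged against the same two benchmarks, above 70% for acceptable and above 80% for excellent. The planned enrolment is 15 (Enrollment). The article describes no measurement or interview for a caregiver who stops before session 6.

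**The concern.** The adherence rule allows for caregivers who take part adequately without reaching session 6. The data-collection rule does not. A caregiver who stops after session 4 or 5 succeeds on Adherence, fails on Assessments, and has no scheduled satisfaction score, post-treatment distress score or interview. A caregiver who stops earlier is lost in the same way.

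Two things are at stake. First, acceptability is a primary outcome, and with 15 participants two or three unmeasured people can decide which side of a benchmark the result falls on. Second, the purpose of the pilot is to refine the manual and procedures from exit interviews before a feasibility randomised trial. Caregivers who stopped may know most about what does not work, and the schedule does not arrange to hear from them. Later analysis cannot recover data that were never sought.

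**Working it through.** The article gives no dropout figure and does not derive the sample size from a formula, so there is no figure of the plan's own to reproduce. The check is a direct count.

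**Inputs.** From the document: N = 15; benchmarks above 70% and above 80%; adherence at 4 of 6 sessions; post measures and interview after session 6. Assumed, because not stated: the number k who reach session 6.

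**Step 1: Adherence against Assessments.** With 15 enrolled, clearing 70% needs 11 caregivers (11/15 = 73.3%; 10/15 = 66.7% is too few). Adherence could therefore be met with nobody reaching session 6. Suppose all 15 complete at least 4 sessions and 5 of them stop at session 4 or 5. Adherence is 15/15 = 100%. Assessments can be at most 10/15 = 66.7%, below the benchmark, even if every questionnaire actually offered was completed in full.

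**Step 2: how likely early stopping is.** If each caregiver independently reaches session 6 with probability p, the chance of at least one early stopper is 1 − p^15, and the expected number is 15(1 − p).

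| Assumed p | At least one early stopper | Expected number |
|---|---|---|
| 0.95 | 54% | 0.75 |
| 0.90 | 79% | 1.5 |
| 0.80 | 97% | 3 |
| 0.70 | 99.5% | 4.5 |

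**Step 3: what a completer-based satisfaction figure says about those enrolled.** Let s be the number satisfied among the k with data. The completer figure is s/k. Over all enrolled, the lower bound is s/15 (no early stopper satisfied) and the upper bound is (s + 15 − k)/15 (all of them satisfied). The table takes the smallest s that clears 70% of k. The last column is the highest Assessments value possible, k/15.

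| k | s | s/k | Range over 15 enrolled | Assessments at most |
|---|---|---|---|---|
| 14 | 10 | 71.4% | 66.7% to 73.3% | 93.3% |
| 13 | 10 | 76.9% | 66.7% to 80.0% | 86.7% |
| 12 | 9 | 75.0% | 60.0% to 80.0% | 80.0% |
| 11 | 8 | 72.7% | 53.3% to 80.0% | 73.3% |
| 10 | 8 | 80.0% | 53.3% to 86.7% | 66.7% |
| 9 | 7 | 77.8% | 46.7% to 86.7% | 60.0% |

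The excellent benchmark behaves in the same way. With 12 completers, 10/12 = 83.3% corresponds to between 10/15 = 66.7% and 13/15 = 86.7% of those enrolled, a range that spans both benchmarks.

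**Step 4: would the loss show elsewhere?** Partly. Assessments is based on enrolled caregivers, so with 10 or fewer completers it fails the 70% mark and warns the reader. With 11 to 14 completers it can still pass, while the satisfaction result over all enrolled remains undetermined around 70%.

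**The case against.** The strongest reply is that this is a condensed article giving the nominal schedule. It does not say that early stoppers are excluded, and an early-termination assessment is the kind of detail often left to the full protocol. The Table 2 caption could be read as a calendar end point, since the program is described as lasting 6 weeks. The satisfaction and credibility questionnaires are also absent from the list of measures in Textbox 2, so it is unclear whether the session-6 sentence covers them. This limits the point to the schedule as written. It does not remove it: the article states a specific trigger, repeats it as the condition for refinement, and sets it beside an adherence rule that does not fit it.

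A reader might infer that the satisfaction denominator is, by definition, those who reached session 6. The documents do not say so. The adherence row uses the same unqualified word, caregivers, and there it cannot mean completers, or adherence would always be 100%. The denominator is ambiguous, and completer-only is what the data schedule would tend to produce.

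A reader might also infer that acceptability is biased upward. That is plausible but not shown. The ranges in the working contain the completer figure, and caregivers may stop because of the patient's course or the burden of care as well as from dissatisfaction. The lower bounds assume that every early stopper is dissatisfied and should not be quoted alone.

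Finally, this is a single-arm Stage IA pilot, its *t* tests are exploratory, and nothing makes the next trial conditional on the 70% mark. That bears on severity and is accepted.

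**Conclusion.** The point holds for the schedule as written, at moderate severity. Caregivers who stop before session 6, including adherent ones, have no scheduled satisfaction score, change score or feedback, and Assessments then records session-6 completion as well as questionnaire feasibility. For illustration, with 11 of 15 reaching session 6 and 8 of them satisfied, a reported 72.7% leaves the figure among those enrolled anywhere from 53.3% to 80.0%. The 11 of 15 is an assumption. The conclusion is that the result would be undetermined; the documents do not establish that it would be too favourable. The loss of refinement feedback does not depend on any assumption about the direction of bias. It needs only that someone stops early, which is more likely than not even if each caregiver has a 95% chance of reaching session 6 (54%, assuming independence).

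**What to change.** In Exit Interview Procedures, state that the post measures and the 5-10 minute interview are sought from every enrolled caregiver: after session 6 or, for those who stop early, at the time of stopping. Make clear that the satisfaction and credibility questionnaires are included. In the Abstract and the article's account of refinement, let early stoppers' interviews feed the revision of the program. If the full protocol already provides for this, one sentence in the article is enough.

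In Table 2, define adherence as at least 4 of 6 sessions among all enrolled. Report satisfaction and credibility over all enrolled, with the number missing and the bounds this implies, beside the figure among those with data. Two alternatives are less suitable. Counting every missing score as a failure, as the only rule, would mix retention into acceptability. A cut-off at session 6 or a fixed date, whichever comes first, could collect post data before a delayed caregiver has finished.

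The cost is protocol wording, a few extra REDCap links or calls, and percentages that may look somewhat less favourable. Some caregivers will decline after stopping, so the number missing still has to be reported. Scores taken at stopping will fall at varying times after baseline and should be identified as such in the pre-post comparison.
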